#### Study Participants

The study population will consist of 250 participants with NSTE-ACS planning to undergo PCI. The diagnosis of patients with NSTE-ACS will be based on the 2011 ESC guidelines. The detailed inclusion and exclusion criteria are listed in Table 1.

**TABLE 1 T1:**
[figure not shown]
Patient Selection Criteria

The APELOT study will be performed in accordance with the ethical principles of the Declaration of Helsinki and will also be consistent with the International Conference on Harmonization and Good Clinical Practice. The study protocol, including the Informed Consent Form, is approved by an Independent Ethics Committee (IEC). The investigator will submit a written approval to the IEC before enrolling any patient into the study. The principal investigator(s) at each center will ensure that the patients were given adequate oral and written information about the purpose, and also possible risks and benefits of the study. Participants will also be notified that they are free to discontinue their participation at any time. The participants will be given the opportunity to ask any questions and time to consider the information provided. The participants’ signed and dated informed consent must be obtained before conducting any specific procedure during the study.

### Data analyses

#### Sample Size Justification

On the basis of onset/offset and respond studies, we expected that a double LD (360 mg) of ticagrelor will result in an absolute increase in IPA of 27% compared with the conventional LD (180 mg) of ticagrelor. With the assumption of a difference of 5.7 and a standard deviation (SD) of 16.344 PRI, and the covariate (baseline PRI) with an *R*^2^ value of 0.2, a total of 114 participants will be required in each arm to achieve a 90% power and a 2-sided alpha of 0.05. Considering a dropout rate of 10%, at least 250 participants would be required to complete the study to reach statistical significance.

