### Study Design and Study Drug Administration

The APELOT trial is an interventional, randomized, open-label, multicenter, phase IV clinical trial that will recruit participants from 8 centers in Beijing, China. All centers would have highly trained experienced personnel. A total of 250 participants with NSTE-ACS who meet the entry criteria will be enrolled and randomized. The flow chart of the study design is shown in Figure 1.

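### On the plan's own inputs, 114 per arm gives about 83% power at two-sided alpha 0.05, not 90%; the figure matches a one-sided 5% calculation

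*Protocol article*

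**What the plan says.** The Sample Size Justification section of the protocol article gives all the inputs together. The effect and variability are set out as "With the assumption of a difference of 5.7 and a standard deviation (SD) of 16.344 PRI". The variance is reduced by adjusting for baseline PRI, with an R-squared of 0.2. From these the article derives its requirement: "a total of 114 participants will be required in each arm to achieve a 90% power and a 2-sided alpha of 0.05".

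It then allows for losses: "Considering a dropout rate of 10%, at least 250 participants would be required to complete the study". The Study Design and Study Drug Administration section uses 250 as the number randomized: "A total of 250 participants with NSTE-ACS who meet the entry criteria will be enrolled and randomized".

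The Statistical and Analytical Plans section sets significance at P below 0.05 and mentions no one-sided test.

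**The concern.** Difference, SD, R-squared, power and alpha together determine the number per arm, so the stated 114 can be checked without any outside information. It comes out about 18% below what a two-sided 0.05 test with 90% power needs on those inputs. Rounding or the choice between a normal and a t calculation cannot explain a gap of that size.

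The statement is the power claim for the primary endpoint, PRI at 2 hours after the loading dose. If it is wrong, the trial has a materially larger chance of missing the effect it was designed to find than the article tells its readers. A non-significant result could then be taken as stronger evidence against a 5.7-point effect than the design supports.

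**Working it through.** **Inputs** (all from Sample Size Justification, except the number randomized, which is from Study Design and Study Drug Administration)

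- Difference d = 5.7 PRI points
- SD = 16.344
- R-squared of baseline PRI = 0.2
- Power 90%, two-sided alpha 0.05
- 114 per arm, equal arms
- Dropout 10%; 250 randomized, which is 125 per arm

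**Formula.** For a comparison of two means adjusted for one covariate:

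n per arm = 2 × (z_alpha + z_beta)² × SD² × (1 − R²) / d²

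The adjusted variance is 16.344² × 0.8 = 267.13 × 0.8 = 213.70, so the residual SD is 14.62. The common factor is 2 × 213.70 / 5.7² = 427.40 / 32.49 = 13.155.

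**Step 1: what reproduces 114.** With one-sided alpha 0.05 and 90% power, (1.645 + 1.282)² = 8.564, and 13.155 × 8.564 = 112.7, so 113 per arm. With the noncentral t (df = 2n − 3), one-sided power is 89.9% at 113 and 90.1% at 114. The one-sided t-based requirement is therefore exactly 114.

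**Step 2: what the stated two-sided test needs.** (1.960 + 1.282)² = 10.507, and 13.155 × 10.507 = 138.2, so 139 per arm. The noncentral t gives 140. The stated 114 is short by 25 or 26 per arm; 25/139 is about 18%.

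**Step 3: power actually available.** Two-sided alpha 0.05, noncentral t:

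| Evaluable per arm | Situation | Power for 5.7 points |
|---|---|---|
| 112.5 | 225 completers (250 × 0.9) | 82.9% |
| 114 | as stated | 83.4% |
| 125 | all 250 evaluable | 86.7% |
| 140 | needed for 90% | 90.2% |

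The normal approximation gives 83.7% at 114 and 86.9% at 125.

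**Step 4: what would have to change for 114 to be right.** At 114 per arm, 90% two-sided power corresponds to a difference of 6.28 points (normal) or 6.30 (noncentral t). With the difference held at 5.7, R-squared would have to be 0.340 (normal) or 0.346 (noncentral t) instead of 0.2.

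**Step 5: other readings tried, normal approximation, alpha 0.05.**

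| Reading | n per arm |
|---|---|
| No covariate adjustment, two-sided, 90% power | 173 |
| SD (not variance) multiplied by 1 − R², two-sided, 90% power | 111 |
| 0.2 read as R (R-squared 0.04), two-sided, 90% power | 166 |
| 0.2 read as R, one-sided, 85% power | 114 |

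The second row misuses R-squared and still does not give 114. The last row gives 114 but contradicts both the stated power and the stated sidedness. Rounding of the difference does not help: 5.65 needs 141 and 5.749 needs 136.

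**The case against.** The strongest objection concerns the cause. A one-sided calculation returns 114, but a match is not proof. The article names no formula or software, and a misprinted input could have the same effect: an R-squared of about 0.34 to 0.35, or a difference of about 6.3, would also lead to 114. If so, the input would need correcting and the 90% could stand. This is fair as far as it goes: the one-sided origin is an inference. It does not affect the finding, because the stated power and the stated inputs are incompatible whichever of them is wrong.

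A second objection is that the design is still reasonable. Power stays above 80%, and if the dropout sentence is read literally, as 250 completers, the shortfall is only about 3 points. The type I error and the analysis are untouched. That is correct, and it is why no extra patients are asked for. But the 86.7% under that reading is still not 90%, and the article attaches the 90% to 114 per arm.

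Third, the planned analysis is a mixed-effects model, whose precision may differ from that of a single-time-point adjusted comparison. The 83% is indeed the power under the article's own sizing method, not necessarily that of the final analysis. But the stated calculation uses no repeated-measures correlation, so the model cannot be called on to justify 114.

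Finally, a null result should be read from its confidence interval, and the article does not plan to infer equivalence from non-significance. The risk of over-reading is therefore a possibility, not a certainty. The understated type II error remains a fact.

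**Conclusion.** The concern holds: the sample-size statement is wrong as written. On the article's own difference, SD and R-squared, 114 per arm gives 83.4% power at two-sided alpha 0.05. The chance of missing a true 5.7-point difference is 16.6%, about 1.7 times the 10% claimed.

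This rests only on the inputs printed in the article, equal allocation, and the standard variance reduction of 1 − R² for a single baseline covariate. The explanation that the calculation was run one-sided at 5% (equivalently, in practice, two-sided at 10%) and labelled two-sided 5% is likely, since it is the only valid form tried that returns 114 at 90% power, but the conclusion does not depend on it.

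**What to change.** Keep the two-sided 0.05 test and the 250 participants, remove the 90% claim, and replace the sentence with wording such as:

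> With 114 evaluable participants per arm, the trial has about 83% power at a two-sided alpha of 0.05 to detect a PRI difference of 5.7 points, assuming an SD of 16.344 and an R-squared of 0.2 for baseline PRI; 90% power corresponds to a difference of about 6.3 points.

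Before the text is issued, the sponsor should look up the original calculation. If it shows that one of the printed inputs is a misprint, that input should be corrected and the power recomputed from it.

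The cost is one sentence and a less favourable stated power, with no added patients and no change to the analysis. The alternative, keeping 90% power on the present inputs, would need 140 evaluable per arm, or 280 in total; with 10% dropout, 280 / 0.9 = 311.1, so 312 randomized in equal arms.

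### The figure of 250 serves as both the number randomized and the number who must complete; 10% dropout leaves 225, and two-sided power is about 83%, not 90%

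*Protocol article*

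**What the plan says.** The Sample Size Justification in the protocol article sets the operating characteristics at "90% power and a 2-sided alpha of 0.05". Its inputs are "With the assumption of a difference of 5.7", "a standard deviation (SD) of 16.344 PRI" and an R-squared of 0.2 for baseline PRI. From these it concludes that "a total of 114 participants will be required in each arm", which is 228 in all. It then moves to the final figure: "Considering a dropout rate of 10%, at least 250 participants would be required to complete the study to reach statistical significance".

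The Study Design and Study Drug Administration section gives 250 a different meaning: "A total of 250 participants with NSTE-ACS who meet the entry criteria will be enrolled and randomized". The Abstract also has 250 as the number randomized, and Study Participants gives 250 as the size of the study population.

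**The concern.** One number is attached to two quantities that differ by the dropout. If 250 are randomized and 10% are lost, 250 cannot complete. The number that remains also falls below the 228 that the paragraph has just called necessary. In addition, a sample size gives a probability of detecting an assumed difference; it does not make a result significant, so the last clause misdescribes what the calculation delivers.

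Checking the dropout step means checking the 228 to which it is applied, and that base figure does not follow from the stated inputs. What is at stake is whether the stated power describes the trial as it will be run. A reader of a null result on the primary endpoint would take it as coming from a trial with 90% power.

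**Working it through.** **Inputs.** From the Sample Size Justification: difference d = 5.7, SD = 16.344, R-squared = 0.2, two-sided alpha 0.05, power 0.90, 114 per arm, dropout 10%. From the Abstract and Study Design: 250 randomized. Assumed here: equal arms (implied by 114 in each), 16.344 is the SD before covariate adjustment, and a dropout is a participant without an evaluable primary measurement.

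**1. The plan's 250.** 2 x 114 = 228, and 228 x 1.1 = 250.8, which is 250 when rounded down. The stated figure is therefore reproduced by adding 10% to the evaluable number.

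**2. Inflation that preserves 228.** N = 228 / (1 - 0.10) = 253.3, or 254 in two equal arms of 127.

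**3. What 250 leaves.** 250 x 0.90 = 225, and 228 - 225 = 3 short. The loss that 250 can absorb is 1 - 228/250 = 8.8%.

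**4. The base figure of 114.** The covariate-adjusted SD is s = 16.344 x sqrt(1 - 0.2) = 14.619. The number per arm is n = 2 x [(z_alpha + z_power) x s / d]^2.

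- Two-sided 0.05, 90% power: 2 x [(1.960 + 1.282) x 14.619 / 5.7]^2 = 138.3, so 139 per arm (140 by noncentral t).
- One-sided 0.05, 90% power: 2 x [(1.645 + 1.282) x 14.619 / 5.7]^2 = 112.7, so 113 per arm (114 by noncentral t).

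The stated 114 is reproduced exactly by the one-sided calculation and not by the stated two-sided one. Other readings at two-sided 0.05 and 90% power do not rescue it. Without the covariate the figure is 173 per arm. Treating 0.2 as R rather than R-squared gives 166. Multiplying the SD by (1 - R-squared) instead of its square root gives 111, which is close to 114 but is not a valid variance adjustment. An R-squared of about 0.34 would be needed for 114 to be right.

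**5. Power at the relevant sizes.** In the normal approximation, power = Phi[d / (s x sqrt(2/n)) - 1.960]. At n = 114 this is Phi[5.7 / (14.619 x 0.13245) - 1.960] = Phi(0.984) = 83.7%. The noncentral t figures (2n - 3 degrees of freedom) are slightly lower:

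| Evaluable in total | Per arm | Power, normal | Power, noncentral t |
|---|---|---|---|
| 225 | 112.5 | 83.3% | 82.9% |
| 228 | 114 | 83.7% | 83.4% |
| 250 | 125 | 86.9% | 86.7% |

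Falling from 228 to 225 costs 83.4 - 82.9 = 0.5 point. The gap between the stated 90% and the 83.4% at 114 per arm is 6.6 points, about thirteen times as large.

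**The case against.** The strongest reply is that the dropout slip is a matter of rounding. Multiplying by 1.1 is a common shortcut, the result is within 4 participants (1.6%) of 254, and 10% is itself a round guess. The Abstract, Study Design and Study Participants all agree on 250 as the number enrolled. On this view the reference to completing is loose phrasing, and because power and alpha are stated explicitly, nothing in the design depends on the clause about significance.

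Most of this stands. The shortfall is immaterial for power, and 250 is most naturally the inflated enrolment figure. A reader might infer that 250 completers are truly required, so that 250 / 0.9 = 278 should be randomized and the trial is 28 short. The document does not support that: the paragraph reaches 250 from 228 by allowing for dropout, and the stronger reading would apply the allowance twice.

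What does not fall away is that the sentence as written contradicts the Study Design section, and that the base of 228 fails on the stated inputs. Condensing a protocol into an article can explain omissions, but nothing is alleged to be missing here: all the inputs are printed and they do not give the printed result.

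**Conclusion.** The point holds, with the weight placed as follows. The text on 250 is inconsistent, and at the plan's own dropout rate it leaves 225 evaluable against 228 required. The cost is about half a point of power, and by itself this calls for a wording correction. The more important error is that 114 per arm gives about 83% two-sided power rather than 90%; about 140 per arm (280 evaluable) would be needed for 90%.

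Two further inferences should be avoided. The loss of 3 participants does not explain the drop from 90% to 83%: randomizing 254 to secure 228 evaluable would still leave 83.4%, and even 250 completers would give only 86.7%. Nor does the match with a one-sided 0.05 calculation show that a one-sided test is intended. The protocol states a two-sided alpha, and the match only suggests how 114 may have arisen.

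The conclusion rests on the stated difference, SD and R-squared being the intended inputs, on equal arms, and on a covariate-adjusted comparison of two means, which is what the paragraph describes.

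**What to change.** Rewrite the end of the Sample Size Justification to say that 250 participants will be randomized, that about 225 are expected to be evaluable for the primary endpoint at 10% dropout, and that this gives about 83% power at two-sided 0.05 under the stated difference, SD and R-squared. In the same edit, replace the claim of 90% power at 114 per arm with about 83%. If only the new sentence were added, the paragraph would give two powers for almost the same sample size. Delete the wording that makes 250 the number who must complete and ties it to reaching significance.

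The cost is one or two sentences and a less favourable stated power, with no extra patients. If the sponsor prefers to keep 90%, that is a different decision: 280 evaluable at 10% loss is 280 / 0.9 = 311.1, or 312 randomized in equal arms.

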#### Statistical and Analytical Plans

Continuous variables will be expressed as mean ± SD or median; and categorical variables will be expressed as frequencies and percentages. We performed statistical analyses using the SPSS version 22.0 (IBM Corp., Amrock, NY). We will use mixed-effects model to compare the pharmacodynamic assessments between the higher LD (360 mg) and conventional LD (180 mg) of ticagrelor. Goodness of fit of the model was assessed using regression and related techniques. Hazard ratio and 95% confidence interval estimates were provided using a Cox proportional-hazards model. Least-squares estimates of the mean difference are statistical significance, considered for *P* values <0.05.

### Implications

The APELOT trial will evaluate whether a high LD (360 mg) of ticagrelor will result in greater platelet inhibition compared with the conventional LD (180 mg) of ticagrelor in NSTE-ACS patients undergoing PCI. Despite optimal evidence-based treatment, NSTE-ACS participants were reported to have worse mid-term and long-term prognoses than STEMI participants with more frequent recurrent ischemic events and a 2-fold higher death rate at 2 years. Effective treatment strategy for such participants is yet to be established. If the APELOT trial confirms a higher LD of ticagrelor will have higher IPA and faster onset before PCI, it would help clinicians to choose the optimal antiplatelet therapy in patients with NSTE-ACS undergoing PCI. In addition, it would facilitate PCI procedures and improve clinical outcomes in patients with NSTE-ACS. The results of this study may have a direct impact on the future treatment for patients with NSTE-ACS, and may pave the way for future treatment recommendations.
